**3. Information about the research participants**

3:1 How are research participants chosen?

Participants will be recruited from schools in Nacka’s more deprived areas: Fisksätra, Orminge and Älta, where the prevalence of overweight and obesity is higher than in other parts of the municipality. Schools in Nacka, where at least 30% of families are considered deprived (inclusion criteria) will be invited to participate in the project. The research group has previously collaborated with Nacka Municipality which has a lot of experience in diet and health promotion work focusing on children and adolescents. Where both parents do not understand Swedish, i.e. if they need an interpreter in order to participate in the motivational interview, the family will be excluded (exclusion criteria). We hope in the future to be able to offer the material translated into several languages and an interpreter to help with motivational session. In this study, however, it is not practical or feasible.

The public health planner from Nacka Municipality will contact principals at the included schools and arrange a time for an initial meeting with the project team. All pre-school classes will be invited to participate. Principals and teachers will be informed by the project team. The project team will inform parents at the annual parent meeting. The parents will then be contacted by letter in tandem with the usual letter from the school health service. Once parents give their consent they are participating in the project. Approximately 14-16 classes from nine different schools will be randomised to either the intervention or control group.

3:2 State the relationship between the researchers/leader of the research and those participating in the research:

Evaluator

3:3 State the statistical foundation with respect to the size of the population(s) and/or

material(s) studied:

Primary outcome is physical activity measured with accelerometry. A “sample size calculator for cluster randomised trials” was used for calculation (Campbell et al, 2004). The estimated sample size was calculated for a two-sided test with the significance level of 0.05 and power was set to 90%. The calculation shows that 12 school classes with a participation rate of 60% in each class, approximately 144 children in total, are needed to detect a 20 % significant increase of physical activity steps between the intervention and control groups. Another outcome in physical activity such as a decrease in sedentary time needs fewer children. It was decided to randomise 200 families in total (100 families in the intervention group and 100 families in the control group) to have a margin for drop-outs and withdrawals.

3:4 State if participants in the research may be included in several studies, either

simultaneously or in another study or other studies closely linked to this one. If so, what

kind of research?

No

3:5 What insurance cover is there for research participants taking part in the project?

The participants are insured within the schools.

3:6 What financial remuneration or other benefits are participants in the research entitled

to and when is this to be paid?

Two lottery tickets

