We will study whether it is possible to improve children’s dietary and physical activity habits and weight development by conducting motivational interviews with parents through the school health care system and by the use of teacher-led classroom-based activities.

Aim

To develop and evaluate a parental support programme delivered in the school health care setting to promote healthy dietary and physical activity habits for parents of 6-year-old children.

Research questions:

How does motivational interviewing with parents, in combination with teacher-led classroom activities, affect children’s dietary habits, physical activity levels, weight development and parental self-efficacy to affect change?

Do children’s dietary habits, physical activity, body weight index (BMI) and parental self-efficacy differ by parental education level?

Research variables:

We aim to study 200 children in 16 pre-school classes in deprived areas in the municipality of Nacka. Half of the classes will be randomised to the intervention group and the other half to the control group.

The primary outcome will be the consumption frequency of certain indicator foods (fruit, vegetables and energy-dense foods) as assessed by questionnaire.

Using an accelerometer, physical activity will be evaluated as total step count per day, the average time in total physical activity over a week, the number of minutes at different intensities and time spent sedentary.

A qualitative study with parents and teachers will be conducted using focus groups and will be analysed using content analysis.

Parental self-efficacy (the ability to affect change and the belief that they are in control) will be evaluated using questions taken from the social cognitive theory.

Secondary outcomes include weight and length data obtained from the school health care journals. Waist circumference is also measured during the school health check-up. Body mass index (BMI) is calculated and overweight and obesity are identified using international cut-offs. In addition, BMIsds is calculated based on Swedish cut-offs.

Knowledge gains:

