Baseline measurements of eating habits (intake frequency of fruit and vegetables and energy-dense products), physical activity habits, inactivity and sleep is assessed by means of a survey (Appendix 5:2). The survey questions are based in part on a validated English parent questionnaire. Parents' self-efficacy, ie, their confidence in their ability to be able to change their children's food and movement habits are measured by a questionnaire (Appendix 5:2). The questionnaire has been translated and modified for use in the area of food and physical activity based on a validated English questionnaire which measures parents' self-efficacy in parenting. Surveys are sent home to parents as soon as consent has been received by the researchers. The questionnaires are then handed in by the parents at the first motivational interview.

The intervention is planned to start in November. During the intervention, the teachers in the intervention classes follow a teacher's manual (Appendix 5:3) which is based on a brochure that has been designed as a result of a scientific review (www.folhalsoguiden.se / food). The brochure is designed to be educational, contains many illustrations and is written in simple Swedish (Appendix 5:4). It is based on the various themes of the review; 1. Good food and meals, 2. Movement/Physical Activity, 3. Candy, snacks, ice cream and soft drinks, 4. Fruits and Vegetables, 5. Advertising, TV and other media, and 6. Sleep and rest. The material contains facts and evidence-based advice to parents. The information in the brochure will form the basis for the future motivational interview. The brochure will be sent home to the families before the intervention starts, so that they have time to reflect on the content before the first motivational interview.

In the pre-school class the teacher will conduct 10 lessons (each 30 minutes in length) described in the teacher manual. Students will be assigned simple home exercises from a workbook on 7 occasions (Appendix 5:5). The purpose of the homework assignments is so that children remind their parents at home about the different themes that have been brought up at school.

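### The protocol names two different primary outcomes, questionnaire food frequency in 2:1 and accelerometer physical activity in 3:3, and sizes the trial only for steps

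*Protocol*

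**What the plan says.** Two sections of the protocol each name a primary outcome.

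- Section 2:1, under the research variables: "The primary outcome will be the consumption frequency of certain indicator foods (fruit, vegetables and energy-dense foods) as assessed by questionnaire".
- Section 3:3, on the statistical basis for the sample size: "Primary outcome is physical activity measured with accelerometry".

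Section 2:1 also describes the accelerometer measures without ranking them: "physical activity will be evaluated as total step count per day, the average time in total physical activity over a week", followed by minutes at different intensities and sedentary time. Its secondary-outcome paragraph begins "Secondary outcomes include weight and length data obtained from the school health care journals" and goes on to waist circumference and BMI. Neither diet nor physical activity appears there as secondary.

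The calculation in 3:3 uses a two-sided 0.05 level and 90% power. It concludes that 12 classes with 60% participation, about 144 children, "are needed to detect a 20 % significant increase of physical activity steps between the intervention and control groups". It adds, without figures, that sedentary time would need fewer children, and it does not mention diet. The number to be randomised is then raised to 200 families to allow for losses. Sections 2:1 and 2:4 plan 16 classes, and 3:1 about 14 to 16.

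Section 2:4 plans two follow-ups with the baseline measurements repeated, one after the intervention at six months and one a year after the start. Neither is named as the primary time point.

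**The concern.** The primary outcome fixes which comparison is confirmatory and what the power statement means. Here two outcomes hold that position in different sections. A report that led with either could cite protocol text in support, whichever way the data fell. If each is tested at the full 0.05, the error rate for the primary claim is no longer 0.05.

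The power statement is affected as well. If 2:1 governs, the trial has no sample-size justification for its primary outcome, because the only effect size in the document concerns steps.

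A secondary consideration bears on which outcome to keep. Intervention parents receive a brochure and interviews that cover the indicator foods, and parents then report those foods. On the instrument, 2:4 says "The survey questions are based in part on a validated English parent questionnaire". The accelerometer does not depend on parental report. This bears on the choice between the two outcomes. It is not part of the contradiction, and it would apply even if diet were the only primary.

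**Working it through.** **1. The two statements side by side.** Section 2:1 gives food frequency from a questionnaire, and 3:3 gives physical activity from an accelerometer. These are different constructs measured by different instruments. Neither section refers to the other. The hypothesis in 2:2 covers diet, activity, weight development and self-efficacy together, so it does not decide between them.

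**2. The plan's own figure.** Inputs from 3:3: 12 classes, 60% participation, 144 children.

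- Children per class: 144 / 12 = 12.
- Implied class size: 12 / 0.60 = 20.

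The head count is coherent. The power calculation cannot be reproduced, because no mean, SD, ICC or class size is given. Under a normal approximation with 12 children per class, 144 children fits a 20% increase for assumed pairs of coefficient of variation and ICC such as 0.37 with 0, 0.30 with 0.05, 0.25 with 0.10 or 0.21 with 0.20. The stated number for steps is neither confirmed nor refuted.

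**3. False-positive rate if either outcome may be called primary.** Each is tested at 0.05.

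- Two independent tests: 1 − 0.95² = 0.0975.
- General bound for two tests: 2 × 0.05 = 0.10.
- Steps plus fruit, vegetables and energy-dense foods tested separately: 1 − 0.95⁴ = 0.185 if independent, and at most 4 × 0.05 = 0.20.

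**4. What the planned trial could detect on an outcome that was not sized.** This is an illustration. The ICC is assumed at 0.01 to 0.10, and there is no adjustment for baseline. With k classes, N children and m = N / k:

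d = λ × √(2 × DE / (N / 2)), where DE = 1 + (m − 1) × ICC,

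and λ is the noncentrality giving 90% power for a two-sided 0.05 t test on k − 2 degrees of freedom.

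| Classes | Children | m | df | λ | d at ICC 0.01 | d at ICC 0.05 | d at ICC 0.10 |
|---|---|---|---|---|---|---|---|
| 16 | 200 | 12.5 | 14 | 3.489 | 0.52 | 0.62 | 0.72 |
| 14 | 200 | 14.3 | 12 | 3.536 | 0.53 | 0.65 | 0.76 |
| 12 | 144 | 12 | 10 | 3.604 | 0.63 | 0.75 | 0.87 |

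For example, with 16 classes and ICC 0.10, DE = 1 + 11.5 × 0.10 = 2.15 and d = 3.489 × √(2 × 2.15 / 100) = 0.72. The first two rows are the planned trial, and the last is the minimum in 3:3.

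**5. Price of keeping both with an equal split.** At 0.025 each, under the normal approximation, a design with 90% power for steps at 0.05 has Φ(3.242 − 2.241) = 0.84. Restoring 90% takes 144 × ((2.241 + 1.282) / 3.242)² ≈ 170 children.

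**The case against.** The strongest reply is that the two statements could be read as undeclared co-primaries. Section 2:1 describes diet and then activity before it turns to secondary outcomes, neither is demoted there, and the hypothesis covers both. That reading is possible, but the protocol does not state it and gives no alpha rule. It would change the repair without removing the need for one.

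Several stronger readings are tempting and are not supported.

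- A reader might infer that the trial is underpowered for diet. The protocol gives no dietary effect size, SD or ICC, so this cannot be shown. The range of 0.63 to 0.87 SD belongs to the 12-class minimum and not to the 14 to 16 classes planned, and adjusting for the baseline measurements could lower the detectable difference further.
- A reader might take 9.75% as a ceiling. It is the value for two independent tests, and the bound is 10%.
- A reader might conclude that the questionnaire is unfit to be primary. Section 2:4 also says that eating habits and self-efficacy are assessed by validated methods. Reporting bias remains a fair concern, but it is separate from the contradiction.
- A reader might suppose that the protocol already points to steps at six months. Section 3:3 names accelerometry in general, only its calculation points to steps, and no follow-up is singled out.

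A separate analysis plan does not answer the point. If it named one primary outcome only, it would contradict one of these two sections.

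**Conclusion.** The point holds as an internal contradiction that must be corrected. Two current sections name different primary outcomes with no rule connecting them, and the 90% power is stated for steps alone. This conclusion rests on the text and needs no assumption.

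The size of the consequence is conditional. The chance of a false-positive primary claim rises from 5% to 9.75% for independent tests, and to at most 10%, if each outcome is tested at 0.05 and either may be reported as primary. It is higher if foods are tested one by one. The detectable difference of about 0.52 to 0.76 SD for the planned design depends on assumed ICCs of 0.01 to 0.10 and no baseline adjustment. It shows what the sponsor would need to justify for diet, and does not show that the trial would fail on diet. Nothing in the document suggests an intention to choose the outcome after seeing results. The fault is that the text leaves this open.

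**What to change.** Before any outcome data are examined, amend sections 2:1 and 3:3 so that both name the same single primary variable and the same time point.

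- **Preferred route.** Make total steps per day by accelerometer the primary outcome, since the trial was sized on it and it is measured objectively, and list the food frequencies as secondary. State which of the two follow-ups in 2:4, six months or one year, is primary.
- **If diet is kept as the primary.** Define one dietary variable and its time point, restrict the 90% power statement to steps, and state the dietary difference detectable with 14 to 16 classes, giving the SD and ICC used.
- **If both are kept.** Declare them co-primary, state the alpha rule and restate the power accordingly. An equal split would leave about 84% for steps at the size that gives 90% now.

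The first route costs only a wording amendment, with no extra children, visits or data. The second also needs a short calculation. The third needs either acceptance of lower power or a larger analysed sample, about 170 against 144 on the normal approximation, which is within the 200 planned but uses part of the margin for losses.

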**4. Information and consent**

4:1 The procedure involved and the content of the *information* that is given when subjects

are asked to participate in the research:

The public health planner from Nacka Municipality will contact principals at the included schools and arrange a time for an initial meeting with the project team. All pre-school classes will be invited to participate. Principals and teachers will be informed by the project team. The project team will inform parents at the annual parent meeting during the spring and autumn of 2010. The parents will then be contacted by letter containing information and a consent form (Appendix 4) in tandem with the usual letter from the school health service at the start of the autumn term 2010. The participants will be informed about the study and that participation is voluntary and that they can withdraw at any point. Many families have an immigrant background so the information will be formulated in simple Swedish to facilitate their understanding and consideration of the information.

4:2 How is *consent* to be obtained and from whom?

Parents of children in pre-school classes in the selected schools will be contacted by letter signed by the project team at Karolinska Institutet, the school physician and public health planner from Nacka Municipality. The letter will inform them about the study's purpose and procedures, and the type of data that will be collected and how the data will be processed. Parents and children will be informed that participation is voluntary and that they can at any time choose to withdraw. The consent form is returned signed by a parent with a pre-paid envelope to the research team who registers either the consent or that they have declined to participate.

Forms will be kept locked in a filing cabinet at Karolinska Institutet.

**5. Considerations in the light of research ethics**

5:1 Describe the risks that participation might entail:

The risk of privacy violation and/or discomfort is judged as minor as is the risk of complications. The accelerometers are worn on the hip attached to a belt and will not involve any discomfort for the children.
The motivational interview will be performed by a person with documented MI skills and will therefore not present a risk of discomfort or pressure.
During the focus group discussions, the various issues will not be intrusive. The moderator and assistant of the discussions will be responsible for ensuring no one is put in a vulnerable situation.

5:2 Describe the predictable benefit for the people participating in the research who are

part of the project (applies especially to treatment):

The project aims to prevent both overweight and disordered eating behavior and thus promote normal weight gain in the children who participate in the project. Many of the families participating in the project are deprived families where obesity is 3-5 times more common compared to families with more resources. Given the uneven distribution of health and obesity which negatively affects deprived groups there is great potential for prevention for the children involved in the project.
The benefits of the project for the parents is that they can get a better understanding of good food and physical activity habits for themselves and their children and may be bolstered in their confidence to bring about change and the ability to set limits.

5:3 and 5:4 In a broader perspective, identify and specify which ethical problems, such as risk versus benefit, can arise as a part of or as a result of the project:

The potential risks are deemed to be very small compared to the benefits in terms of improved health of children and families.
There is always a risk with this type of project in which a group might feel singled out (deprived). This must be weighed against benefits in terms of improving health among these children.
The risk that parents could be made to feel like bad parents is considered small because the person who will conduct the motivational interviews has documented experience.
Overall, the benefits outweigh the risks.

**6. Presenting the results**

6:1 How are both the entity principally responsible for the research and research

collaborators guaranteed access to data (to be stated when the research is commissioned) and who is responsible for processing data and writing reports?

The principal investigator, [name], will be responsible for data collection, data processing and report writing. Researchers at Karolinska Institutet will have access to data. Results will be published jointly by the research team.

6:2 How will the results be made publicly available? Will the study be sent for publishing in

a journal or published in some other manner?

Results will be made public via the publication of reports and in scientific journals in 2011 and 2012. Results will also be presented at national and international congresses in 2011 and 2012. A manual will be developed in 2011 and 2012 for the school health services regarding how schools can develop parental support for promoting healthy food and physical activity habits.

6:3 In what manner will the right to integrity of those participating in the research be

guaranteed when the material is made public or is published?

Reporting is completely anonymous which means that no names will be listed and that participating individuals cannot otherwise be identified. The results are reported on group level. Name and address information is encoded with a serial number and stored in a locked cupboard, separate from the data file, during and after the study.

**7. Reporting the financial circumstances and dependencies**

7:1 When the research is commissioned:

N/A

7:2 Give an account of any financial agreements with a responsible body or any other financiers

(name, amount):

N/A

7:3 Give an account of the interests of the responsible research body, the principal researcher and of participating researchers:

N/A

**9. List of annexes**

Please see original document in Swedish
